## Abstract

**Background:**

Sepsis caused by complicated intra-abdominal infection is associated with high mortality. Loss of endothelial barrier integrity, inflammation, and impaired cellular oxygen have been shown to be primary contributors to sepsis. To date, little is known regarding the pathway for the mobilization of endothelial progenitor cells (EPCs) from the bone marrow in sepsis whereas stromal-cell-derived factor 1a (SDF-1a) and hypoxia inducible factor 1 (HIF-1) seem to have a role in the EPC response to hypoxic microenvironments.

The aims of the study are: (a) to determine the time course of the levels of circulating EPCs (CD133/CD34), SDF-1a, and HIF-1 in septic patients undergoing major abdominal surgery (group S), (b) to investigate the relationship between CD133/CD34, HIF-1, and SDF-1a, and (c) to investigate the relationship of these factors with the outcome of group S patients treated with standard conventional therapy alone (CT) or with the addition of extracorporeal hemoperfusion therapy (HCT).

**Methods/design:**

Patients undergoing major abdominal surgery will be allocated into groups: postoperative non-septic patients in an emergency surgical ward (group C) and postoperative septic patients in an intensive care unit (group S). The latter will be randomized to receive CT alone (S1) or with HCT (S2). Healthy volunteers (group H) will be recruited at University Hospital Foggia.

Peripheral blood (PB) samples will be collected preoperatively (T0), at 24 h (T1), 72 h (T2), 7 (T3), and 10 (T4) postoperative days in groups S and C, and at T0 in group H. The CD34/133 cells and HIF-1 counts will be determined by flow cytometer analysis. The concentration of SDF-1a in plasma will be calculated by enzyme-linked immunosorbent assay analysis (ELISA).

**Discussion:**

This prospective randomized clinical trial is designed to investigate circulating stem cells, levels of HIF-1 and SDF-1a, and their interrelationship in septic postoperative abdominal surgical patients treated with CT alone or with HCT. The rationale is that an integrated understanding of the role of hypoxia-related factors and EPCs in PB of septic patients could indicate which molecular processes need to be regulated to recover the innate immunity homeostasis. Understanding the function of EPCs in sepsis may provide innovative diagnostic and therapeutic approaches to improve the prognosis of this syndrome.

**Trial registration:**

ClinicalTrials.gov: NCT02589535. Registered on 28 October 2015.

**Electronic supplementary material:**

The online version of this article (10.1186/s13063-018-2556-0) contains supplementary material, which is available to authorized users.

## Background

Complicated intra-abdominal infection is a frequent cause of sepsis and septic shock in intensive care unit (ICU) patients [1, 2]. Sepsis caused by intra-abdominal infection is associated with higher mortality ranging on average 30% to 60% because of (a) the broad spectrum of infection and disease severity, (b) the crucial role of surgery in the management of intra-abdominal infection, and (c) the ongoing emergence of multidrug resistance in pathogenic organisms [3–6].

Evidence supports that the pathophysiology of sepsis moves from an initiating early/acute hyperinflammatory phase to a late/chronic hypoinflammatory and immunosuppressive phase [7]. More recently, loss of endothelial barrier integrity, inflammation, and impaired cellular oxygen have been shown to be primary contributors to sepsis-related organ dysfunction [8]. Endothelial progenitor cells (EPCs), a specific subtype of hematopoietic stem cell, are mobilized into the peripheral circulation under various pathologic conditions that are associated with vascular injury [9–14]. Mutunga et al. observed an increase of circulating endothelial cells during sepsis and concluded that endothelial damage occurs [9]. However, the quantification of EPCs in septic patients has had controversial results and Cribbs et al. demonstrated that the increased levels of EPCs were inversely associated with organ dysfunction [15]. To date, little is known regarding the relationship between EPC and organ dysfunction in septic postoperative abdominal surgical patients.

In addition, the pathway for the mobilization of EPCs from the bone marrow (BM) in sepsis or septic shock is still unknown. Emerging evidence suggests that stromal-cell-derived factor 1a (SDF-1a) mediates the migration of hematopoietic stem cells from BM to peripheral blood (PB), while hypoxia inducible factor 1 (HIF-1), which regulates SDF-1a expression, is the central mediator of the cellular response to hypoxic microenvironments [16].

### Aims of the study

Primary objective: To determine the time course of the levels of circulating EPCs (CD133/CD34), SDF-1a, and HIF-1 in septic patients undergoing major abdominal surgery.

Secondary objective 1: To investigate the relationship between CD133/CD34, HIF-1, and SDF-1a.

Secondary objective 2: To investigate the relationship between CD133/CD34, HIF-1, SDF-1a, and the outcome of sepsis and septic shock patients treated with standard conventional therapy alone (CT) or with the addition of extracorporeal hemoperfusion therapy (HCT).

In this trial, we hypothesize that levels of CD133/CD34, HIF-1, and SDF-1a will increase in septic surgical patients as a consequence of impaired tissue perfusion and cellular hypoxia. Our hypothesis is that the stimulation of hypoxia-related factors, like SDF-1a and HIF-1, could be the primary step in the stimulation of BM stem cells. Furthermore, we assume that surviving septic patients will show higher levels of EPCs, HIF-1, and SDF-1a.

## Methods/design

### Recruitment

This prospective observational clinical trial is designed to target postoperative patients undergoing major abdominal surgery and healthy volunteers at University Hospital Foggia. Participants who meet pre-specified eligibility criteria (Table 1) and provide written informed consent will be enrolled in the study.

**Table 1 Tab1:** Eligibility criteria

Inclusion criteria	Exclusion criteria
Caucasian Over 18 years of age	When it is impossible to collect blood samples (organizational reasons or because of emergencies regarding the health of the patient)
	Pregnant patients
	Organ transplantation
	Palliative care
	Metastatic cancer patients

Detailed information on the benefits and risks of taking a blood sample will be provided to study candidates. Human blood samples and therapies will be acquired in accordance with institutional guidelines. All patients will be managed by applying standard protocols, following current guidelines and recommendations. The diagnosis of sepsis and septic shock will be made according to the new definitions [17].

This study is to be performed in accordance with the *World Medical Association Declaration of Helsinki: Ethical principles for medical research involving human subjects* (WMA 20 2013) [18], the *International Ethical Guidelines for Biomedical Research involving Human Subjects* (CIOMS 2002) [19], and the *ICH Harmonised Tripartite Guideline: Guideline for good clinical practice* (ICH 1996) [20].

The study has been approved by the local research ethics committee (Comitato Etico of Ospedali Riuniti, Foggia, Italy, 69/CE/2015). The trial has been registered with ClinicalTrials.gov (NCT02589535). We adhered to the SPIRIT statement (Additional file 1).

### Study design

Each day, the anesthesiologist in the operating room and the on-call anesthesiologist will alert the principal investigator to potential eligible patients. Participants included in the trial will be divided into two groups:Group C: Postoperative non-septic patients in an emergency surgical ward (control group)Group S: Postoperative septic shock patients in an ICU

Using a computer-generated sequence of numbers, patients in group S will be randomly assigned to receive either conventional therapy for septic shock alone (CT) as per the Surviving Sepsis Campaign guidelines (S1) or standard therapy plus extracorporeal hemoperfusion therapy (HCT) with polymyxin B-immobilized polystyrene-derived fibers to remove endotoxins from the blood (S2) [21]. Healthy volunteers (group H) will be recruited from among staff members of the University Hospital Foggia (Figs. 1 and 2).

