### Statistical analysis

The power analysis suggested that a sample size of 30 patients per group is required to detect a higher percentage of total circulating EPCs (CD133+/CD34+ cells as a percentage of all myelomonocytic cells) in septic patients vs ICU controls (assuming α = .05 and power = .95) [22]. A sample size of three patients per group is required to detect higher SDF-1 levels in the septic vs control groups (assuming α = .05 and power = .95) [10]. This number is increased to 33 per group to allow for a 20% drop-out rate.

The normality of the distribution will be assessed by the Shapiro–Wilkinson test. If the data are normally distributed, they will be expressed as mean (± standard deviation). The data will be analyzed using the repeated measurements analysis of variance. Differences between the groups at each time point will be examined post hoc using an independent sample *t* test. A paired sample *t* test will be used to detect changes within the groups. The level of statistical significance was chosen as *P* < .05. The statistical analysis will be performed with the Statistical Package for the Social Sciences (SPSS Inc., Chicago, IL) version 15.0 for Windows.

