## Discussion

The proposed study is a prospective observational clinical trial designed to investigate in septic postoperative abdominal surgical patients: (a) levels of circulating stem cells, HIF-1, and SDF-1a; (b) the interrelationship among stem cells, HIF-1, and SDF-1a; and (c) the correlation of those factors with outcomes for septic postoperative abdominal surgical patients treated with CT alone or with HCT. The rationale is that a deep and integrated molecular understanding of sepsis at the system level will indicate which molecular processes need to be regulated to recover the innate immunity homeostasis.

A potential limitation is that blood samples will be not collected in those patients operated on as an emergency over night or when the laboratory is closed, since the HIF-1 analysis requires immediate collection-to-storage times of fresh blood samples [23].

Understanding the function of EPCs in sepsis and sepsis-related organ dysfunction may provide innovative diagnostic and therapeutic approaches for this devastating syndrome.

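### Group S is randomised between two treatments, but the article also calls the study observational, sizes S as one group, and names no T0-adjusted comparison of the arms

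*Protocol article*

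**What the plan says.** **Design.** Study design uses a computer-generated sequence: "patients in group S will be randomly assigned to receive either conventional therapy for septic shock alone (CT"), arm S1, or that therapy with added polymyxin B hemoperfusion, arm S2. The Abstract's Discussion paragraph agrees: "This prospective randomized clinical trial is designed to investigate circulating stem cells". Recruitment says "This prospective observational clinical trial is designed to target postoperative patients", and the main Discussion opens with "The proposed study is a prospective observational clinical trial designed to investigate in septic postoperative abdominal surgical patients".

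**Objectives.** The primary objective (Aims of the study) is the marker time course in septic surgical patients, with no mention of arm. The arms appear only in secondary objective 2, which relates the markers to outcome under either treatment.

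**Size.** Statistical analysis gives 30 per group for septic patients against controls (alpha 0.05, power 0.95), raised to 33 per group for drop-out. It gives no figure for S1 against S2 and no allocation ratio.

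**Tests.** The main analysis is a repeated-measures ANOVA. Then "Differences between the groups at each time point will be examined post hoc using an independent sample" t test, and paired t tests are used for change within groups. The word groups is not defined here as S and C or as S1, S2 and C. Blood sampling provides a preoperative T0 sample and four later ones (T1 to T4) in S and C.

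**The concern.** Hemoperfusion is given to alter the septic process whose markers are being followed. If S is analysed as one group, the septic curve after T0 depends on the effect of hemoperfusion and on the S1:S2 split. It then describes neither septic patients on conventional therapy nor those on the combined treatment.

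S1 against S2 is the only comparison in the study protected by randomisation. It has no stated size, and none of the named tests compares the arms with adjustment for the baseline value that is already being collected. The conflicting design labels leave a reader unsure whether a randomised comparison is intended at all.

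**Working it through.** **Inputs.** From Statistical analysis: 30 per group, alpha 0.05, power 0.95, 33 per group after a 20% drop-out allowance. Effect size, SD, sidedness, allocation ratio within S and correlation with T0 are not given. Assumed below: two-sided tests, SD of 1, 1:1 allocation, correlation r of 0.3 to 0.7.

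**1. The plan's own figure.** Without an effect size the 30 cannot be reproduced, only inverted:

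d = (1.960 + 1.645) × √(2/30) = 0.93 SD, or 0.95 SD with the t distribution. A one-sided test gives 0.85 to 0.86.

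The 33 does not follow from 30 and 20% either, since 30/(1 − 0.2) = 37.5, rounded up to 38. That is a separate matter. It is used here only to bound the arm sizes: 33 × 0.8 = 26.4, or about 13 per arm.

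**2. Effect of pooling S.** Let hemoperfusion shift a marker by τ SD in half of S. The pooled difference is 0.93 + τ/2, the SD in S is √(1 + τ²/4), and power at 30 per group is Φ(difference / √[(1 + SD²)/30] − 1.960).

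| τ (assumed) | S − C difference | SD in S | Power |
|---|---|---|---|
| −0.5 | 0.68 | 1.03 | 74% |
| −0.25 | 0.81 | 1.01 | 87.5% |
| 0 | 0.93 | 1.00 | 95% |
| +0.25 | 1.06 | 1.01 | 98% |
| +0.5 | 1.18 | 1.03 | 99.5% |

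**3. S1 against S2, unadjusted two-sided t test.**

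| Patients per arm | Basis | Detectable at 80% power | Power for d = 0.95 | Power for half of it |
|---|---|---|---|---|
| 13 | 33 in S less 20% | 1.15 SD | 64% | 21% |
| 15 | 30 in S | 1.06 SD | 71% | 24% |
| 16 | 33 in S | 1.02 SD | 74% | 25% |
| 16.5 | 33 in S | 1.01 SD | 75% | – |

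With a one-sided test, the detectable difference at 16 per arm is 0.90 SD. If 33 per group meant 33 in each arm, power for d = 0.95 would be 97%, but the text does not say so.

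**4. Adjusting for T0.** The variance of the comparison is multiplied by 1 − r². At 16 per arm and 80% power (normal approximation), the detectable difference is (1.960 + 0.842) × √(1 − r²) × √(2/16).

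| r (assumed) | Variance cut | Detectable difference |
|---|---|---|
| 0 | 0% | 0.99 SD |
| 0.3 | 9% | 0.94 SD |
| 0.5 | 25% | 0.86 SD |
| 0.7 | 51% | 0.71 SD |

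**The case against.** Several stronger readings are tempting, and the document does not support them.

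- **The tests ignore T0.** Too broad. Repeated-measures ANOVA can take T0 as a time level and the paired tests can measure change from it. Only the t tests at each time point leave it out. Measured against change from T0, with variance 2(1 − r), the gain from adjustment at r = 0.7 is 0.60/0.51, a factor of about 1.18, not 1/0.51 = 1.96. At r = 0.5 it is 1.33 on either basis.
- **S will be pooled.** This is the natural reading, because Study design speaks of two groups and only septic against control is powered. It is not stated for the model, and model terms may be set out in a fuller plan. A course averaged over treatments is also a legitimate descriptive target, though one that depends on an unstated allocation ratio.
- **Hemoperfusion weakens the primary comparison.** The direction is unknown. The authors expect survivors to have higher marker levels, so an effective treatment could raise them and increase power.
- **The arm comparison is an underpowered objective.** A treatment effect on marker levels is not a stated objective; secondary objective 2 concerns markers and outcome. This stands, and it is the reason to label the contrast exploratory.
- **Arm effects will be read from separate paired tests.** The plan says only that these tests look at change within groups. The clause in the fix is a precaution.
- **Candidates are told only about the blood sample.** Recruitment says "Detailed information on the benefits and risks of taking a blood sample will be provided to study candidates", but it does not say that nothing else is explained, and it requires written consent. Consent material is not in the text available, so no finding can rest on this.

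An unadjusted randomised comparison is also unbiased, so T0 adjustment is a gain in precision and not the removal of an error.

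**Conclusion.** The point holds in a limited form. The design labels contradict each other, and this can be read directly from the text. The primary objective and sample size take S as a single group although its patients are randomised to two treatments. On that reading the septic course after T0 is a mixture, and the power of S against C could move either way (74% to above 99% for shifts of 0.5 SD). No stated test is a T0-adjusted comparison of S1 with S2, and at 16-17 per arm that contrast can detect only about 1.0 SD.

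All the power figures rest on an effect size inverted from n = 30, two-sided testing and 1:1 allocation. The gain from adjustment rests on an assumed correlation. This is a worthwhile improvement to interpretability and precision. It does not invalidate the study.

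**What to change.** 1. Fit group as C, S1 and S2 with a group-by-time term. Report the septic time course by arm, and give a pooled S curve only alongside the two arm curves.
2. Compare S1 with S2 on the T1 to T4 values adjusted for T0, by ANCOVA or a mixed model with T0 as covariate. Do not infer a difference between arms from separate paired tests within each arm.
3. State the allocation ratio and the number in each arm. Label S1 against S2 exploratory and give its detectable difference.
4. Reconcile the design label in Recruitment and the main Discussion with Study design and the Abstract, for example as a randomised comparison nested within a cohort.

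The cost is a wording change plus one factor and one covariate. T0 is already collected and arm is known from the allocation, so no new data are needed. Recruitment is reported as ongoing, so the change can be made before analysis. The drawback is that each arm's curve rests on fewer patients than a pooled curve and will be less precise.

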**Fig. 1 Fig1:**
[figure not shown]
Work flow for the study. After recruitment, the participants will be allocated into one of two groups: postoperative septic patients in an intensive care unit (group S) or postoperative non-septic patients in an emergency surgical ward (group C). Healthy volunteers (group H) will be recruited from among staff members of University Hospital Foggia

**Fig. 2 Fig2:**
[figure not shown]
Schedule of enrolment, interventions, and assessments

### Blood sampling

PB samples will be collected in sterile evacuated blood collection tubes with anticoagulant ethylenediaminetetraacetic acid (EDTA; 3 ml) at the following time points:preoperatively (T0), at 24 h (T1), 72 h (T2), 7 (T3), and 10 (T4) postoperative days in groups S and CT0 in group H

The absolute numbers of leukocytes and lymphocytes in PB will be determined at the same time with an automatic cell counter (Cell-Dyn 3500, Abbott Diagnostics, Santa Clara, CA, USA). Peripheral whole blood samples (100 μl) will be used for fluorescence-activated cell sorting (FACS) analysis, and the plasma samples will be collected and stored at −80 °C.

Biochemical tests will be determined daily, according to the routine procedure in the surgical ward and ICU, and performed in the laboratories at University Hospital Foggia, according to the institutional guidelines.

Demographic, anamnestic, clinical, and laboratory data will be recorded.

### Flow cytometry

The samples of whole blood (100 μl) will be stained within 1 h from taking the blood sample. To analyze the viability of the cells, they will be stained with 7-aminoactinomycin D (7-AAD), which will bind to the DNA of cells that are undergoing or have undergone apoptosis (Stem Kit™ Beckman Coulter, Brea, CA, USA). The cell surface staining will be performed by adding the following fluorochrome-labeled monoclonal antibody reagents: fluorescein isothiocyanate (FITC)-conjugated anti-CD34 (Beckman Coulter, Brea, CA, USA) and phycoerythrin (PE)-conjugated anti-CD133 (Miltenyi Biotech, USA). Staining will be performed according to the manufacturer’s guidelines.

Cells will be fixed and permeabilized using the BD Intrasure kit (Becton Dickinson, Franklin Lakes, NJ, USA) and intracellular staining of HIF-1 will be performed using HIF-1 alpha (Alexa Fluor® 647 anti-human HIF-1α Antibody, BioLegend Inc., CA, USA) following the manufacturer’s instructions. The samples will be resuspended in phosphate-buffered saline and analyzed with a FACS Caliber flow cytometer (Becton Dickinson, Franklin Lakes, NJ, USA) and FCS3 software. Cell will be acquired with a four-parameter flow cytometry method (CD34 FITC/CD133 PE/CD45 PerCP/ HIF-1 ACP staining, side, and forward angle light scatter). The flow cytometer will be calibrated every 24 h and quality controls performed according to the UK National External Quality Assessment Service protocol. The number of CD34/CD133/HIF-1 cells in PB will be calculated as the count of absolute lymphocytes times the percentage (%) of gated CD34/CD133 positive cells, and expressed as absolute number of cells per 1 μl PB.

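### The cell-count formula has no HIF-1 term, and the EPC variable it yields is not the one the sample size was based on

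*Protocol article*

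**What the plan says.** The primary objective (Aims of the study) is "To determine the time course of the levels of circulating EPCs (CD133/CD34), SDF-1a, and HIF-1 in septic patients undergoing major abdominal surgery". Secondary objective 1 is "To investigate the relationship between CD133/CD34, HIF-1, and SDF-1a". Both treat HIF-1 as a variable separate from the EPC level. The abstract does the same: "The CD34/133 cells and HIF-1 counts will be determined by flow cytometer analysis".

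The Flow cytometry section describes an intracellular HIF-1 stain, acquired in its own channel alongside CD34, CD133 and CD45. It then gives the article's only derivation rule for these variables. It opens with "The number of CD34/CD133/HIF-1 cells in PB will be calculated" and defines that number as "calculated as the count of absolute lymphocytes times the percentage (%) of gated CD34/CD133 positive cells", in cells per microlitre. The population in which the percentage is taken is not named.

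On the counts available, the Blood sampling section says: "The absolute numbers of leukocytes and lymphocytes in PB will be determined at the same time". No myelomonocytic count is listed.

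The Statistical analysis section requires 30 patients per group for EPCs, with α = .05 and power = .95, and defines EPCs there as "CD133+/CD34+ cells as a percentage of all myelomonocytic cells".

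**The concern.** There are two separate problems.

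**HIF-1.** The rule names HIF-1 in the quantity to be calculated but not in the calculation. Applied as written, it gives the CD34/CD133 count under a HIF-1 label. One of the three primary biomarkers would then have no derivation, and the EPC–HIF-1 relationship in secondary objective 1 would carry no information.

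**EPC.** The trial is sized on a percentage with a myelomonocytic denominator, while the derived variable is an absolute count with a lymphocyte multiplier. Scale and reference population both differ, so the stated power does not describe the variable that the rule produces. The unstated gate adds to this: a percentage times a count is a cell count only if both refer to the same population.

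**Working it through.** **Notation.** L is the absolute lymphocyte count per μl (Blood sampling). p is the gated CD34/CD133 positive proportion (Flow cytometry). h is the HIF-1 positive proportion of the same parent population, and f is the HIF-1 positive fraction of the CD34/CD133 cells. The article gives no values for any of these.

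**1. The count rule.** As written, N = L × p. The compound label can be read in two ways. For this step, assume that L is the right parent count.

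- Triple-positive cells: the target is L × p × f. The rule overstates it by (L × p)/(L × p × f) = 1/f. For assumed f this is 10 at f = 0.1, 2 at f = 0.5 and 1.11 at f = 0.9. It is correct only at f = 1.
- A separate HIF-1 count: the target is L × h. The rule does not contain h.

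On either reading the rule returns L × p for HIF-1 and L × p for EPC, so their correlation is exactly 1.

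**2. The stated sample size.** The 30 per group cannot be reproduced forward, because the article gives a citation but no mean, SD or effect size. It can be inverted with the normal approximation for two means, d = (z for α + z for power) × √(2/n), where √(2/30) = 0.2582:

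- two-sided: (1.960 + 1.645) × 0.2582 = 0.93
- one-sided: (1.645 + 1.645) × 0.2582 = 0.85

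The article does not state whether the test is one- or two-sided. Both values of d refer to the myelomonocytic percentage.

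**3. From the percentage to the count.** On the log scale, log(L × p) = log L + log p. The group difference gains the group difference in log L, and the variance gains the variance of log L plus twice its covariance with log p. If p has a myelomonocytic denominator, as in the power statement, none of these added terms is given. If p is taken in another gate, its own distribution is unknown too. Power for the count may therefore be higher or lower than .95, and no corrected sample size can be computed.

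**4. The multiplier.** If p is taken within a lymphocyte gate, L × p is a valid concentration. If p is the myelomonocytic percentage, the matching multiplier is the myelomonocytic count M, and using L understates the count by M/L. With assumed L of 500 to 2000 and M of 4000 to 16000 per μl, that ranges from 4000/2000 = 2 to 16000/500 = 32. The article does not say which case applies.

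**5. Two counts sharing one multiplier.** Once HIF-1 has its own term, the EPC and HIF-1 counts still share the parent count. Suppose the two percentages are independent of each other and of the parent count, with log-SD sP each, and the parent count has log-SD sL. The log-scale correlation is then sL²/(sL² + sP²). For assumed sL = 0.5:

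- sP = 0.5: 0.25/(0.25 + 0.25) = 0.5
- sP = 1.0: 0.25/(0.25 + 1.00) = 0.2

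**The case against.** The strongest defence is that the sentence is compressed shorthand for one method applied to each gated population, and that an article leaves gating detail to a laboratory procedure not shown. HIF-1 has its own antibody and channel, and both the abstract and the aims treat it separately. This is plausible, and it rules out one stronger inference: nothing shows that the investigators intend to analyse one number under two names. It does not remove the point. The article states a rule, that rule does not produce the quantity it names, and no other rule for HIF-1 is given.

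A reader might also infer more than the article supports on three matters.

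- **That the lymphocyte multiplier is wrong.** This joins the multiplier to a denominator found only in the power statement, which rests on a cited study and need not describe this trial's gating. CD45 and light scatter are acquired, so a lymphocyte gate is possible. What stands is that the gate is unstated.
- **That the septic-versus-control contrast in EPCs could change sign because of lymphopenia.** With assumed leukocytes of 15 versus 9 and lymphocytes of 0.8 versus 1.5 (×10⁹/l), equal leukocyte percentages give a count ratio of 15/9 = 1.67, while the formula gives 0.8/1.5 = 0.53. This needs a leukocyte gate that the article does not state, equal percentages in both groups, and cell counts that are assumed. With a lymphocyte gate there is no such distortion.
- **That correlating two counts is invalid, or that HIF-1 should become a percentage or fluorescence intensity.** If the gate matches the multiplier, both counts are real concentrations, and relating them is a legitimate aim. Replacing the stated HIF-1 count would be a preference. The 0.2 to 0.5 range above rests on assumed SDs and supports only an additional analysis.

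**Conclusion.** The point holds in two parts, neither of which needs assumed values.

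First, the stated rule does not yield a HIF-1 count. Followed literally, it makes HIF-1 identical to EPC and empties that pair in secondary objective 1. SDF-1a, measured by ELISA, is not affected.

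Second, the 30 per group at power .95 belongs to the myelomonocytic percentage, where it implies a standardised difference of about 0.93 two-sided or 0.85 one-sided (normal approximation, equal groups). It cannot be claimed for the absolute count per μl.

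The multiplier is a conditional matter: valid with a lymphocyte gate, otherwise mismatched. The 1/f and M/L factors only illustrate possible size, over assumed ranges.

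**What to change.** 1. Name the parent population of the gate and replace the single rule with two:
   - EPC per μl = count of the parent population × % CD34+CD133+ of that population.
   - HIF-1 count per μl = the same parent count × % HIF-1 positive of that population, or × % CD34+CD133+HIF-1+ if triple-positive cells are meant. Say which.
2. Align the power statement with the analysis. Either analyse the myelomonocytic percentage as the EPC variable that was powered, or state that the 95% power applies only to that percentage and not to the absolute count.
3. For secondary objective 1, keep the counts and add a supporting analysis that relates the percentages, since two counts sharing a multiplier are correlated in part through it.

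The cost is minor rewording and a little extra analysis, with a power claim limited to the percentage scale. Leukocyte and lymphocyte counts and the HIF-1 channel are already acquired. If the parent gate is myelomonocytic, its absolute count is not among those listed, and the article must say how it is obtained. Recruitment was under way at publication, so the definitions should be fixed before the data are analysed.
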